### Data management

Each participant will receive a unique identifier upon study entry. This identifier will be used for all data documentation to ensure the participant’s confidentiality. Data will be gathered in source documents and then transferred onto paper case report forms. Later, all data will be digitized and stored in a central database. To improve accuracy of data entry, entries will be verified for proper format and expected range as well as double-checked. Overall data quality will be assured by independent monitoring throughout the study. However, due to the minimal risks of our dietary interventions, a data monitoring committee is deemed unnecessary. Data will be stored for 10 years after study completion and then deleted. Any modification to the current study protocol will be submitted to the institutional review board, all trial participants and the trial investigators.

We only obtain consent for usage of data and samples for the research question described in this protocol. Thus, we do not intend to use participant data or biological samples in ancillary studies.

Results will be personally explained to all study participants, presented on national and international conferences, published in peer-reviewed journals, and disseminated to neurologists and the medical laity. We will comply with the official eligibility guidelines for authorship for all publications and do not intend to use professional writers.

### Data analysis

Confirmatory analysis will be conducted based on the intention-to-treat (ITT) population. The aim is to show that KDs and FDs are superior to the SD, meaning that the number of new T2 lesions after 18 months of dietary intervention adjusted for the baseline value is lower in the KD and FD groups than in the SD group. Although the sample size calculation was conservatively based on the Mann–Whitney *U* test, the final analysis of the primary endpoint will be based on non-parametric analysis of covariance (ANCOVA) on ranks with the treatment group as a fixed factor and adjustment for the baseline number of T2 lesions. The resulting coefficients will be reported with 95% confidence intervals and their corresponding *p*-values compared to a two-sided Bonferroni-adjusted significance level of 0.025 [48].

We do not plan any interim analyses. In the case of more than 5% missing for the primary endpoint, we plan to replace missing values in the outcome parameter using multiple imputation [49] under the missing at random assumption in addition to the complete case analyses.

As a sensitivity analysis, the primary endpoint will be analyzed in the per-protocol population. This population includes all randomized patients who meet the study eligibility criteria and fulfill all compliance criteria throughout the study.

We intend to perform two subgroup analyses, men vs. women and MS medication vs. no MS medication, by adding another main effect for sex or medication, respectively, as well as an interaction term. These subgroup analyses will be analyzed in an exploratory manner to generate possible hypotheses for follow-up studies without adjustment for multiple comparisons. For these, *p*-values may not be interpreted as confirmative.

Safety analysis will include calculation of frequencies and rates of adverse and serious adverse events within 18 months of the interventions.

Secondary endpoints will be analyzed in an explorative manner and descriptives will be given using the mean and standard deviation for sufficiently normal distributed metric variables, the median with limits of the interquartile range (IQR: 25th and 75th percentiles) for skewed metric or ordinal data, as well as absolute and relative frequencies for count data.

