## Introduction

Multiple sclerosis (MS) is the most common chronic inflammatory autoimmune disease of the central nervous system. It leads to neurodegeneration and is a major cause of progressive disability and early retirement in young adults [1–3]. According to estimates, more than 2 million people worldwide are affected [4]. Relapsing–remitting MS (RRMS) is the most common form of MS and is characterized by relapses and periods of remission as well as systemic inflammation of the central nervous system and progressive neurodegeneration from the earliest disease stages [5, 6].

Currently, there is no cure for MS, but several immunomodulatory therapies are available that may slow disease progression [7]. However, all of them may have substantial side effects and patients respond differently due to the complex nature of the disease. Consequently, there is a need for complementary therapies such as specific diets that may reduce MS symptoms, improve the patient’s quality of life and even delay disease progression. A recent review reported that up to 70% of MS patients already use alternative and complementary medicine [8].

It is widely accepted that a combination of genetic susceptibility and environmental factors causes MS [9]. That nutrition might be among these factors is supported by the fact that MS is more frequent in western countries than in less-developed nations [10]. The so-called western diet is high in energy, saturated fats and sugars. Of note, a meal high in fat and refined carbohydrates has been shown to cause a more pronounced postprandial insulin secretion and enhanced inflammation compared to a meal high in fiber and fruits in healthy lean subjects [11]. In line with this, a 12-week ketogenic diet (KD) decreased insulin resistance and several serum inflammatory markers in overweight men and women [12].

These are important findings since insulin resistance seems to be more common in MS patients than in healthy controls and is associated with higher Expanded Disability Status Scale (EDSS) scores [13, 14]. Furthermore, elevated serum levels of the pro-inflammatory cytokine IL-17 in MS patients [14] may contribute to the impaired glucose and insulin metabolism in MS [15].

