### Randomization

Eligibility of patients will be determined at the screening visit by a trained physician. Afterward, randomization is done in three strata to distribute possible confounding factors equally to the dietary interventions. Strata are sex (man or woman), MS medication (yes or no) and lesion load (< 15 or ≥ 15 lesions) in the baseline brain MRI scan. We use a stratified block randomization with variable block length. This will ensure a homogeneous distribution of interventions over these strata. An external statistician who is not involved in the study carries out the randomization according to predefined randomization lists.

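### The primary rank ANCOVA omits sex and MS medication, two of the three stratification factors; if they predict new T2 lesions, the test is conservative and some power is forgone

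*Protocol article*

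**What the plan says.** Under Randomization, the Protocol article states: "Strata are sex (man or woman), MS medication (yes or no) and lesion load", the last split at 15 lesions on the baseline scan. The method is given as "We use a stratified block randomization with variable block length", and the purpose as "to distribute possible confounding factors equally to the dietary interventions".

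Under Data analysis, the confirmatory model is an ANCOVA on ranks in the ITT population, "with the treatment group as a fixed factor and adjustment for the baseline number of T2 lesions". Each diet is compared with the standard diet at a two-sided 0.025. The two subgroup analyses, by sex and by medication, extend this model "by adding another main effect for sex or medication, respectively, as well as an interaction term". They are labelled exploratory.

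On whether medication matters for the outcome, the Introduction says only that "several immunomodulatory therapies are available that may slow disease progression". No effect size is given for sex or for medication.

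**The concern.** Three factors are balanced by design and one is carried into the primary model, through the baseline T2 count. The subgroup wording confirms that sex and medication are absent from the primary model, since each has to be added there. No reason is given.

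Blocking within strata removes chance imbalance in the stratifiers, so the treatment contrast varies less from one randomization to the next. A model without those factors does not know this and leaves their variance in the residual. If they are prognostic, the reported standard error exceeds the true one, the test rejects less often than its nominal level under the null, the intervals are too wide and power is lower than it could be. At stake is precision in the trial's only confirmatory test, not its validity.

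**Working it through.** **1. The plan's own sample size.** Inputs from Power calculation: P = 0.72, two-sided α = 0.025, power 80%, 10% dropout, 37 per group. Noether's formula for the Mann–Whitney test:

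n = (z₀.₉₈₇₅ + z₀.₈₀)² / [6 (0.72 − 0.5)²] = 32.73, so 33 per group.

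Power at 33 is Φ(√(6·33)·0.22 − z₀.₉₈₇₅) = 80.4%. With 10% dropout, 33/0.9 gives 37 per group and 111 in total. The plan's figures reproduce, and they assume no covariate adjustment.

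**2. Analytic effect of leaving the factors out.** Let R² be the share of residual rank variance that sex and medication explain once baseline T2 count is in the model. R² is not in the documents and is an assumed range. With balanced strata the true standard error is √(1 − R²) times the one reported. Write c = z₀.₉₈₇₅ and δ = √(6·33)·0.22. Then:

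- actual α, planned model: 2[1 − Φ(c/√(1 − R²))]
- power, planned model: 1 − Φ((c − δ)/√(1 − R²))
- power with both factors: Φ(δ/√(1 − R²) − c)

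| R² | reported SE / true SE | actual α, planned model | power, planned | power, both factors | forgone (points) |
|---|---|---|---|---|---|
| 0 | 1.00 | 0.025 | 80.4% | 80.4% | 0 |
| 0.05 | 1.03 | 0.0215 | 81.0% | 82.5% | 1.5 |
| 0.10 | 1.05 | 0.018 | 81.6% | 84.7% | 3 |
| 0.20 | 1.12 | 0.012 | 83.0% | 88.9% | 6 |
| 0.30 | 1.20 | 0.007 | 84.6% | 92.8% | 8 |

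**3. Simulation: what lesion-rate ratio between medicated and unmedicated patients would matter?** Common set-up: eight strata, blocks of 3 or 6, negative binomial counts with shape k (larger k means less overdispersion), least squares on ranks, rejection at 0.025. The share medicated, k and the treatment effect are assumptions.

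*Setting A and setting B*: 60% medicated and a 60% reduction in lesions. A has 99 patients analysed. B has 111 randomized, 10% random dropout and no sex effect. Power is shown as planned model → model with both factors.

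| medicated / unmedicated lesion rate | setting | k = 1 | k = 2 |
|---|---|---|---|
| 1.0 | B | 59.9 → 59.2% | 81.2 → 81.1% |
| 0.8 | B | 59.1 → 58.9% | 80.6 → 80.7% |
| 0.7 | B | 59.6 → 60.1% | 81.5 → 82.0% |
| 0.5 | B | 53.2 → 54.6% | 76.6 → 79.7% |
| 1/2 | A | 57 → 59% | 77 → 80% |
| 1/3 | A | 51 → 56% | 70 → 76% |
| 1/4 | A | 46 → 54% | 62 → 74% |

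Under the null in setting A, the planned test rejects at about 0.020–0.021, 0.015–0.017 and 0.009–0.012 for ratios 1/2, 1/3 and 1/4. A further run with dropout at a ratio of 0.33 gave 5 to 7 points of power and null rejection of 0.010–0.020.

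*Setting C*: 99 patients, mean count 3, 30% men, 65% medicated, and a sex effect wherever medication has one (log rate ratio 0.2 at the mildest step, 0.3 otherwise). The treatment rate ratio is 0.37 for k = 1 and 0.55 for k = 4.

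| log rate ratio, medication (as ratio) | k = 1 | k = 4 |
|---|---|---|
| 0 (1.00) | 69.2 → 69.2% | 68.3 → 68.2% |
| −0.4 (0.67) | 67.2 → 67.8% | 64.8 → 66.8% |
| −0.7 (0.50) | 66.8 → 69.5% | 59.5 → 66.2% |
| −1.1 (0.33) | 63.2 → 68.2% | 48.7 → 64.6% |

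At k = 1 this agrees with A and B. With less dispersed counts (k = 4) and a sex effect as well, the gains are larger: 2.0, 6.7 and 15.9 points. In the most extreme case (k = 4, ratio 0.33, null) the planned model's mean reported standard error is 6.92 against an empirical 5.66, and it rejects 0.6% of the time.

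Absolute power in these runs reflects the assumed treatment effect and dispersion. Only the differences within a row bear on this point.

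**The case against.** The strongest reply is that the size is unknown and may be negligible. The documents call the strata only possible confounders and give no figure for their prognostic strength. Medication is not randomized here. Every entrant, treated or not, must have had a relapse or a new or enhancing lesion in the last two years, so treated entrants may be those with breakthrough activity, and the treated–untreated contrast may be smaller than drug efficacy would suggest. The yes/no factor also pools all therapies. The stratifier closest to the outcome, lesion load, is already adjusted for. The simulated conservatism depends on block lengths that the plan gives only as variable, and on reading the ANCOVA on ranks as least squares on ranks, since the cited method is not shown.

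All of this stands as a limit on size. It does not remove the point: the omission is fixed in the text, its direction is certain if either factor is prognostic, and including the factors costs essentially nothing if neither is.

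A reader might go further and infer that standard errors are certainly too large, or that medication is the strongest available predictor of new lesions. The documents support neither. They suggest an influence of medication without ranking or quantifying it.

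**Conclusion.** The point holds conditionally, as a low-cost gain in efficiency. The loss is nil if sex and medication do not predict new T2 lesions given the baseline count. It is about 0 to 3 percentage points of power if medicated patients have 0.5 to 0.7 times the lesion rate, and about 5 to 12 points only at a three- to fourfold difference. These ranges assume 60% medicated, k of 1 to 2 and a 60% treatment effect. The k = 4 runs with an added sex effect show that less dispersion and a second prognostic factor can push the loss above them.

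Two stronger conclusions are tempting and do not follow. First, the confirmatory test is not invalid: the omission neither biases the comparison nor inflates type I error, so a positive result would remain sound. Second, the trial does not fall below its planned 80% because of this. The 33 per group come from an unadjusted Mann–Whitney calculation that reproduces, and with P held at 0.72 the planned model keeps 80.4% to 84.6% power over the R² range examined. The loss is relative to a model that matches the randomization.

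**What to change.** Before outcome data are seen, add sex and MS medication (yes/no, as used for stratification) as fixed factors alongside treatment group and baseline T2 count in the primary rank ANCOVA. Use the same model in the ITT, imputed and per-protocol runs. Each subgroup model then adds only its interaction term, because the main effects are already present.

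The cost is a wording change in the protocol or analysis plan and two degrees of freedom. With 99 patients analysed, the residual degrees of freedom go from 99 − 4 = 95 to 99 − 6 = 93. No extra patients or data are needed, because both variables are recorded for randomization. The timing matters: the same change made after the results are known would look data-driven.

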### Power calculation

Based on the results of other MS studies in our research center in comparable patient cohorts, an average of three new T2 lesions after 18 months is expected in the SD group. Sample size was calculated with the Wilcoxon (Mann–Whitney) rank-sum test and the significance level was adjusted (Bonferroni) for the two comparisons (KD vs. SD and FD vs. SD). With a sample size of 33 patients per group and a two-sided significance level of 0.025, there is a power of 80% to detect a probability of 0.72 that an observation from group 1 is smaller than that from group 2. This corresponds to a standardized effect size of 0.83 and an expected mean difference in the number of new T2 lesions in each of the intervention groups of 0.5 compared to the SD group after 18 months (Query Advisor 7.0). We expect a dropout rate of approximately 10% and therefore plan to enroll 37 patients per group, 111 patients in total.

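### The primary 95% confidence intervals do not match the 0.025 level at which the two confirmatory comparisons are tested, and are not labelled unadjusted

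*Protocol article*

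**What the plan says.** One sentence in the Data analysis section of the protocol article sets two levels for the primary endpoint. For estimation: "The resulting coefficients will be reported with 95% confidence intervals". For testing, the p-values of those same coefficients are "compared to a two-sided Bonferroni-adjusted significance level of 0.025".

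The Power calculation section uses the same test level. It describes the significance level as "adjusted (Bonferroni) for the two comparisons (KD vs. SD and FD vs. SD"), and the design is stated as "With a sample size of 33 patients per group and a two-sided significance level of 0.025".

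The Data analysis section calls the subgroup and secondary analyses exploratory. It gives no such qualification for the intervals on the primary endpoint, and no 97.5% or otherwise adjusted interval appears anywhere in the article.

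**The concern.** A two-sided test at level α and a (1 − α) interval from the same coefficient and standard error give the same answer about zero. At α = 0.025 the matching interval is 97.5%. A 95% interval matches α = 0.05, which is the per-comparison level that the Bonferroni step was introduced to replace.

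When a p-value falls between 0.025 and 0.05, the report will show an interval clear of zero beside a comparison that has failed its confirmatory test. The authors then have to explain the discrepancy after the results are known, and a reader who goes by the interval may take it as evidence of superiority that the plan does not grant. At stake is the consistency of the primary result as reported; the validity of the test is not in question.

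**Working it through.** **Inputs.** From the Power calculation section: two comparisons against a shared SD arm, two-sided 0.025 each, 33 per group, 80% power, P(X<Y) = 0.72, standardized effect 0.83, about 10% dropout, 37 enrolled per group. From the Data analysis section: 95% intervals and a threshold of 0.025. My assumptions: the rank-ANCOVA coefficient is approximately normal, and the two test statistics have correlation 0.5 (equal arms, shared control).

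**1. The plan's own figures reproduce.**
- Bonferroni: 0.05/2 = 0.025.
- Noether's formula for the Wilcoxon–Mann–Whitney test: N = (z₀.₉₈₇₅ + z₀.₈₀)² / [12 × 0.25 × (0.72 − 0.5)²] = (2.241 + 0.842)² / (3 × 0.0484) = 65.46, so 32.7 and hence 33 per group. Power at 33 per group is 80.4%.
- Standardized effect: √2 × z₀.₇₂ = 0.824, against the stated 0.83.
- Dropout: 33/0.9 = 36.7, so 37 per group; 3 × 37 = 111.

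The 0.025 level is therefore built consistently into the design. Only the interval level departs from it.

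**2. Critical values.**
- The 95% interval excludes zero when |Z| > 1.960.
- The confirmatory test succeeds when |Z| > 2.241.
- Width ratio: 2.241/1.960 = 1.144 (1.147 with t on 107 degrees of freedom).

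Interval and test disagree when 1.960 < |Z| ≤ 2.241. The reverse disagreement cannot occur: if |Z| > 2.241, the 95% interval also excludes zero.

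**3. Example.** Z = 2.10 gives p = 0.036, so the comparison fails at 0.025. In standard-error units the 95% interval starts at 2.10 − 1.96 = +0.14 and excludes zero. The 97.5% interval starts at 2.10 − 2.24 = −0.14 and includes it.

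**4. How often the two disagree, per comparison.** This is P(1.960 < |Z| ≤ 2.241) with Z normal, mean μ, variance 1.

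| True effect in SE units (μ) | Probability |
|---|---|
| 0 (null) | 0.05 − 0.025 = 2.5% |
| 2.1 (near the maximum) | 11.2% |
| 3.083 = 2.241 + 0.842 (exactly 80% power) | 6.9% |
| 3.3 | 5.5% |
| 3.5 | 4.2% |

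Under the global null, the chance that at least one of the two comparisons disagrees is about 4.8% (simulation, correlation 0.5).

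**5. Familywise error under the global null, correlation 0.5.**

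| Rule | Either direction | Favouring KD or FD only |
|---|---|---|
| p < 0.025, as the plan states | 4.65% | 2.3% |
| 95% interval excludes zero, which the plan does not adopt | 9.1% | 4.5% |

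With independent comparisons, the two-sided figure for the second row would be 1 − 0.95² = 9.75%.

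**The case against.** The strongest reply is that the decision rule is clear and sound. Superiority is judged from p-values against 0.025, no sentence makes the interval a criterion, and familywise error is about 4.65%. This stands. A reader might infer from the mismatch that the trial's type I error is inflated to about 9%. The document does not support that: 9.1% belongs to a rule that the protocol does not adopt, and it counts exclusions of zero in both directions. Counting only those that favour an intervention diet, the misreading gives 4.5% against 2.3%.

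A reader might also infer that interval and test can contradict each other in either direction, or that the plan promises 95% joint coverage. Neither holds. The disagreement runs one way only, and the article never calls the intervals simultaneous.

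Pointwise 95% intervals beside a multiplicity-adjusted test are a legitimate choice when labelled as such. A condensed article can leave some labelling to the full protocol or the SAP, neither of which is shown. But the article is not silent here: it sets both levels in one confirmatory sentence and leaves the intervals unqualified, so an SAP that followed it would carry the mismatch forward.

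Finally, the 6.9% assumes exactly 80% power. The article describes its Mann–Whitney sizing as conservative relative to the planned ANCOVA; if power is higher, the figure falls, as the table shows. If the true effect is smaller than planned, it can rise to about 11%.

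**Conclusion.** The point holds as a minor reporting mismatch. For each of the two confirmatory comparisons, the reported interval is the one that belongs to a 0.05 test, while the test is made at 0.025, and the article does not tell the reader so. For p between 0.025 and 0.05 the interval excludes zero although superiority is not shown. No test, alpha allocation, sample size or decision rule is wrong.

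The mismatch follows from the two stated levels and depends on no assumption beyond interval and test coming from the same model and standard error. Its probabilities (2.5% under the null, about 6.9% at exactly 80% power) rest on the normal approximation. The familywise figures (4.65% as planned, 9.1% if the intervals are misread as tests) also rest on the correlation of 0.5.

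**What to change.** Report 97.5% confidence intervals for KD vs SD and FD vs SD on the primary endpoint. An interval excluding zero and p < 0.025 then become the same event. If 95% intervals are also shown, state that they are unadjusted and play no part in the confirmatory decision. Exploratory secondary and subgroup results can keep 95% intervals, labelled unadjusted.

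This is a small wording change to the Data analysis section, to be carried into the SAP if it repeats the sentence, and best made before the data are analysed. The price is primary intervals about 14% wider. Sample size, test and trial conduct do not change.

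### Holm's step-down would give more power for the second diet than plain Bonferroni, within the same 0.05 familywise bound (an efficiency gain, not an error in the plan)

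*Protocol article*

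**What the plan says.** In the protocol article, Methods, Data analysis, the confirmatory p-values from the rank ANCOVA are each held against a "two-sided Bonferroni-adjusted significance level of 0.025". The same paragraph gives the aim: "The aim is to show that KDs and FDs are superior to the SD". It reports the coefficients with 95% intervals.

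The Power calculation section names the family of hypotheses: "the significance level was adjusted (Bonferroni) for the two comparisons (KD vs. SD and FD vs. SD"). It sizes the trial at the same level: "With a sample size of 33 patients per group and a two-sided significance level of 0.025", there is "power of 80% to detect a probability of 0.72 that an observation from group 1 is smaller than that from group 2". The expected difference is assumed for each intervention group, so the plan expects both diets to work.

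The article mentions no step-down, closed or hierarchical procedure. Whatever the first comparison shows, the second is tested at 0.025.

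**The concern.** With two hypotheses, Holm's procedure tests the smaller p-value at 0.025 and, only if that is rejected, the other at 0.05. It needs no assumption about dependence, so the shared SD arm is no obstacle, and it keeps the familywise error at or below 0.05. Every rejection under Bonferroni is also a rejection under Holm.

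Suppose KD gives p = 0.01 and FD gives p = 0.04. Under the plan FD is not declared superior; under Holm it is, with the 0.05 familywise guarantee intact. The stated aim covers both diets, and a joint success is where the single-step rule loses most. The stake is power for the second diet, in a trial whose Discussion names cost and staffing as prominent reasons why such studies are scarce.

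**Working it through.** **Inputs from the Power calculation section.** Two-sided level 0.025 per comparison; power 80%; probability 0.72; 33 evaluable per group; 10% dropout; 37 per group and 111 in total.

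**Assumption, not stated in the article.** The two test statistics have correlation 0.5. With equal arms of size n and a common variance σ², each difference from SD has variance 2σ²/n and the two share the SD mean, with covariance σ²/n. Hence (σ²/n)/(2σ²/n) = 0.5. Simulated rank-sum statistics gave 0.47 to 0.49.

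**Step 1: reproduce the plan's own figure.** Noether's formula for the rank-sum test is n per arm = (z for 1−α/2 + z for power)² / [6(p − 0.5)²].

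- z(0.9875) = 2.241, z(0.80) = 0.842, sum 3.083.
- n = 3.083² / (6 × 0.22²) = 9.505 / 0.2904 = 32.73, rounded up to 33. Power at 33 is 80.4%.
- Dropout: 33/0.9 = 36.7, rounded up to 37; 3 × 37 = 111.
- At two-sided 0.05 the formula gives 27.03, so 28 per arm. The stated N therefore does rest on 0.025.

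The design reproduces.

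**Step 2: compare the two rules at the same n.** Let T1 and T2 be bivariate normal with correlation 0.5 and mean 3.083 where a diet has the planned effect.

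- Bonferroni rejects each hypothesis if |T| > 2.241.
- Holm also rejects one hypothesis if its |T| lies between 1.960 and 2.241 and the other |T| exceeds 2.241.

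The gain per comparison is the probability of that extra region. The gain for both diets is twice it, because either diet can be the second. Results from 4,000,000 draws (numerical integration agrees within 0.1 percentage point):

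| Both diets at the planned effect | Bonferroni | Holm |
|---|---|---|
| Power per comparison | 80.0% | 84.6% |
| Power to show both superior | 68.8% | 77.9% |
| Power to show at least one | 91.3% | 91.3% |

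The gains are 84.6 − 80.0 = 4.6 points and 77.9 − 68.8 = 9.1 points.

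**Step 3: vary the effect.**

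- Both diets at half the planned effect: per comparison 24% to 27%; both 11% to 17%.
- One diet at the planned effect, the other at 75% of it: power for the weaker diet 52.9% to 61.6%.
- One diet at the planned effect, the other at 50% of it: power for the weaker diet 24.2% to 32.9%.

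**Step 4: type I error.**

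- Neither diet works: familywise error 4.6% under both rules.
- One diet works at the planned effect, the other is inert: false-positive rate for the inert diet 2.5% under Bonferroni, about 4.2% under Holm.
- The effective diet at 1.5 times the planned effect: 4.9% under Holm. In the limit of an overwhelming effect: 5.0%.

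**Step 5: check with the sizing test.** Three-arm rank-sum trials (60,000 simulated, 33 per arm, normal shift 0.83) gave 83.5% to 88.0% per comparison, 73.6% to 82.5% for both, and 93.4% unchanged for at least one. Absolute power is somewhat higher than in Step 2, and the gains are about the same.

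**Step 6: the gain in patients.** Under the model of Step 2, Bonferroni needs about 39 evaluable per arm to match Holm's power for both diets. With 10% dropout that is 39/0.9 = 43.3, so 44 per arm and 3 × 44 = 132 in total, against 111.

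**The case against.** The strongest reply is that nothing here is wrong. Bonferroni is valid under any dependence, is prespecified, and is used consistently in sizing and analysis. The plan sets itself 80% power per comparison at 0.025 and reaches it. It sets no target for showing both diets superior, so the largest gain concerns a criterion it did not power. All of this stands. It bears on how serious the point is, not on whether Holm would do better.

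A reader might go further and infer one of three things that the article does not support:

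- **That the type I control or the sample size is faulty.** Step 1 reproduces N, and the familywise error stays below 0.05.
- **That Holm's familywise error is the same in every scenario.** Only the 0.05 bound and the rate with two inert diets are the same. Bonferroni protects an inert second diet more strictly, at 2.5%; the 4.2% under Holm is the value at the planned effect, not a ceiling.
- **That a second diet with p = 0.04 is refused with no error-control reason at all.** The stricter protection just described is a reason, although the 0.05 familywise guarantee does not require it.

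Bonferroni also has simple matching simultaneous 97.5% intervals, which Holm lacks. That advantage is real, but the plan reports 95% intervals beside a 0.025 test and so does not use it.

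Finally, the gain is conditional: it arises only when one p-value is at or below 0.025 and the other lies between 0.025 and 0.05.

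**Conclusion.** The point holds as a cheap improvement in efficiency. Under the same 0.05 familywise bound, Holm adds about 4.6 points of power per comparison and about 9.1 points for showing both diets superior, which is the stated aim. It adds nothing to the chance of showing at least one.

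These figures assume that both diets reach the planned effect and that the test statistics are correlated at about 0.5. They shrink with smaller effects. The planned rank ANCOVA may change absolute power, but not which rule rejects more. Against the gain stands a higher false-positive rate for an inert second diet, up to 5.0% instead of 2.5%. The article's multiplicity control and sample size are sound as they stand.

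**What to change.** Keep the 0.025 sizing, 37 per group and 111 in total. Before unblinding, specify for the confirmatory analysis that the smaller of the two p-values (KD vs SD, FD vs SD) is tested at two-sided 0.025 and, if it is rejected, the other at two-sided 0.05. Report 97.5% intervals for both comparisons and flag any hypothesis rejected only at the second step.

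The cost is one sentence and no further patients. There are two downsides to accept knowingly. One is the higher false-positive rate for the second diet when only one works. The other is that a second-step rejection may stand beside a 97.5% interval that includes no difference. If the sponsor prefers the stricter protection and simple matching intervals, keeping Bonferroni is defensible; the intervals should then be reported at 97.5%.
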